#### **4.1.2 Bone Mineral Density (BMD)**

A baseline DXA scan within the last two years will be required for all women prior to randomisation. If there is a delay in receiving the test results, an extension of up to 6 months may be obtained with prior approval from one of the IBIS II Steering Group co-chairmen. The DXA scan can be performed at any site and use of portable DXA machines that examine the forearm are acceptable. A detailed sub study will investigate bone parameters in greater detail in selected centres. In these centres bone mineral density measurements will be taken in approximately 1,000 women by DXA scans at baseline, and years 1, 3, 5, and 7 to examine the changes in BMD during and after treatment. Full details of investigators and procedures can be found in the separate bone sub study protocol. (Please note: as of Sept 2010 the bone sub-study is closed for recruitment.)

#### **4.1.3 Spinal Radiograph**

A baseline radiological assessment must be carried out within two years prior to randomisation to rule out low trauma vertebral fractures. If there is a delay in receiving the test results an extension of up to 12 months may be obtained with prior approval from one of the IBIS II Steering Group co-chairmen. The spinal radiograph requires two x-rays in one lateral dimension to view the thoracic and the lumbar vertebrae. These must be reported on by a qualified radiologist and the report must be available before randomisation takes place. If there are more than **TWO** low trauma vertebral fractures, then the woman cannot take part in any of the IBIS-II protocols. (The European Prospective Osteoporosis Study (Epos) Group, 2002).

Note: If the spinal x-ray report states that there is wedging of more than 20% then this should be considered equivalent to one fragility fracture.

## **4.2 Personal and medical details**

A questionnaire giving height, weight, smoking habits, selected clinically relevant medical history and risk factors for breast cancer must be completed for all women entering the study – entry Case Report Form (CRF).

Information on prescriptions and hospital visits (other than those directly associated with the study) will be recorded in order to facilitate an assessment of additional costs or savings to the health service related to long term use of tamoxifen or anastrozole. It is difficult to estimate what the outcome of this analysis will be at this stage, since the costs of diagnosing and treating some side effects may be more than offset by reductions in other areas.

## **4.3 Samples and Specimens**

### **4.3.1 Blood samples**

Women will have a sample of 14ml (2 x 5ml SST tubes and 1 x 4ml EDTA tube) venous blood taken at entry and 10 ml (2 x 5ml SST tubes only) will be taken at years 1 and 5 as clotted whole blood. 4ml of the entry sample will be put into the EDTA tube provided and used to look for susceptibility genes to breast cancer or side effects. In the UK, both tubes will be posted immediately by first class postage in pre-addressed SARSTEDT t-box containers to St. Mary's Hospital, London. All samples except the EDTA sample must be spun down locally before posting. Follow-up samples will be treated identically except that the EDTA tube will not be required. Bloods will be stored at -70°C and analysed retrospectively, mostly on a case-control basis in an anonymous fashion. They will be used to evaluate biomarkers, which are potential but not yet established markers for risk of disease or response to the preventive therapies under study. The follow-up blood samples will also be used to monitor compliance in a sample of women. The blood samples will remain the property of the Steering Group.

Arrangements for non-UK centres will be made in collaboration with the IBIS Co-ordinating Centre on an individual basis, with frozen aliquots being sent in dry ice to London for long-term storage on a regular basis as agreed at the site initiation visit and in the site contract.

### **4.3.2 Pathology specimens**

A set of representative diagnostic H&E stained slides plus the original hormone receptor assay slides (ER and/or PgR) will be required for central review from those patients entering the study after mastectomy for DCIS (entry criterion 16). Paraffin blocks containing representative areas of the tumour will also be requested. The latter will be used to make additional slides and tissue arrays, and will be returned to the sender. If possible, the pathologist should be made aware of the woman's involvement in the IBIS-II Study before blocks are taken. It may then be possible to make extra blocks and slides specifically for study purposes. If blocks are not available, 10 unstained sections on uncoated slides should be provided. A standard DCIS Pathology Entry Form must be completed for each specimen and this is included in the case report forms. In addition, a copy of the original pathology reports (and a copy of the UK Sloane form, where available) must be provided. Diagnostic slides and paraffin blocks will be requested for all breast, endometrial, or ovarian cancers developing after trial entry. These samples will be used for central pathology review and marker studies, and will remain the property of the Steering Group, who will be responsible for deciding how they will be used in any further projects.

### **4.3.3 Saliva samples**

Women who did not provide a baseline EDTA blood sample should be approached to request a saliva sample used to look for susceptibility genes to breast cancer or side effects. There is a separate Patient Information Sheet and Consent Form for this. The IBIS-II CCO will inform sites of eligible participants to this part of the protocol and sites will be asked to call participants to inform them of this request and obtain verbal consent. If the participant agrees to this, sites will send out a saliva kit to be collected at home. Together with the kit, the PIS and CF for this process will be sent to the participant along with instructions for providing the saliva sample. Participants will be asked to read and keep the PIS, sign and date the CF and post it with the saliva sample to the IBIS-II CCO in the freepost addressed pack provided.

The saliva samples will be analysed for the same biomarkers as the EDTA blood samples and will remain the property of the Steering Group.

## **4.4 Sub Studies**

Measurements of changes in hormone levels, lipid profiles, bone biomarkers, and endometrial biopsies will be made in selected centres and will be considered as separate studies and are not addressed in this protocol. Data collection will be kept at a minimum and only items that are essential to analyse the specific endpoints listed below will be collected. All protocols for special studies will be submitted to the Steering Committee for information and co-ordination. A special detailed study on the quality of life and cognitive function will also be undertaken in selected centres. These studies will require appropriate Ethics Committee approval.

## **4.5 Management of Trial Participants**

### **4.5.1 Follow-up**

#### **4.5.1.1 Active Treatment Follow-up (Baseline-Month 60)**

Women will be seen in clinic at six months and one year in their first year of participation. Then they may be seen annually with an option to attend for a six monthly visit as well. All women may also be contacted by their Local Coordinator every six months to offer ongoing support and information as necessary during the five years of treatment, but no data is required for the study at these contacts.

Advice on maintaining healthy bones (e.g. calcium and vitamin D supplementation, sunlight and weight bearing exercise) will be offered to all women in the trial. Treatment with bisphosphonates should be considered where necessary. The use of raloxifene or any other SERM, or HRT for osteoporosis or any other reason is not permitted in this trial. Interested general practitioners (GPs), and those within the vicinity of a centre, will be sent the study protocol and information leaflets, as these GPs will be very important both for recruitment and for support during the study, which should help with compliance. Blood samples (10ml) to document changes in biomarkers and to monitor compliance will be taken at year 1 and year 5. Mammograms will be taken at intervals, as described in section 4.1.1. These will be reviewed centrally on a subset to examine the effects of treatment on mammographic opacities.

#### **4.5.1.2 Post-treatment Follow-up Questionnaires (PTQ) - Years 6 – 10**

After 5 years of active treatment, women will continue to be followed up for clinical events of interest including SAEs, via the 'post-treatment follow-up' CRF for a further 5 years.

These will specifically ask the patients about the following events: -

- Breast cancer and DCIS (endpoint not requiring reporting)
- Stroke or TIA
- Other cancers (except basal cell carcinoma, squamous cell carcinoma of the skin and carcinoma in situ of the cervix)
- Cardiovascular events e.g. angina, heart attack, hypertension
- Thromboembolic events e.g. deep vein thrombosis, pulmonary embolism, phlebitis
- Osteoporosis/Broken/fractured bone
- Deaths

The decision to collect events of interest rather than asking about all AEs is based upon the following

- 5x half-life of IMPs will be reached within 35 days i.e. a short time period and therefore long term monitoring is not required.
- Except for certain conditions (endometrial cancer, osteoporosis/fracture, cardiovascular disease), further side-effect either stop with IMP washout or are of negligible significance.
- The safety profiles of Anastrozole has already been well-established across multiple trials and long follow up periods (as of 31 July 2016, the total cumulative exposure figure for ARIMIDEX in the marketed setting is calculated to be in excess of 8 million patient years)
- This is an ageing trial population with many AEs meeting the definition of SAEs but that are not of direct relevance to the trial objectives. To date, approximately 6% of reported SAEs in the post-treatment phase have been defined as causally related by the site investigator. Efforts should be re-focused on the collection of events known to be IMP related and the identification of any emerging safety signals. A more defined scope of AE collection is therefore warranted.

- All identified SARs/SUSARS will meet expedited reporting timeframes.

Sites have the option to conduct this by clinic, phone, postal questionnaire or if the patient is not able to be contacted, consultation of hospital records. This will collect data required to meet the primary, secondary and exploratory objectives of the trial.

Prior to the implementation of amendment 60, the above procedures were completed at all sites. Following the implementation of amendment 60, open international sites continue to follow this procedure, while patients from closed UK and international sites are followed up via digital registries as described in section 4.5.1.4.

#### **4.5.1.3 Post- treatment Follow-up Questionnaires (PTQ) - beyond 10 years**

The 16 year follow-up results from the IBIS-I Trial (Cuzick et al, 2015) was seminal in determining the long-term benefits of tamoxifen as prophylaxis for breast cancer. This confirmed that “the risk-reducing effect of tamoxifen appears to persist for at least 10 years, but most side effects of tamoxifen do not continue after the 5-year treatment period”. Collection of breast cancer occurrence for extended follow up periods (beyond 5 years) will be pivotal in determining if the effect of anastrozole, like tamoxifen, can persist for at least 10 years.

The ATAC trial 10 year follow-up results (Cuzick et al., 2010) extended the previously reported superior efficacy of anastrozole over tamoxifen. Furthermore, results demonstrated a carryover benefit for recurrence in the hormone-receptor positive population, which is larger than that previously shown for tamoxifen. This highlights the need for continued long term follow-up in IBIS-II, collecting breast cancer occurrence data up until the end of trial definition in 2022. Published results from this trial (Cuzick *et al.* 2014) have already been published at median average follow up of 5 years (IQR 3·0–7·1), 40 women in the anastrozole group (2%) and 85 in the placebo group (4%) had developed breast cancer (hazard ratio 0·47, 95% CI 0·32–0·68,  $p < 0·0001$ ). Sustained

follow up is required to see if this difference persists and in the case of similar tamoxifen trials, may further diverge.

Sites should continue to follow-up those participants that have reached 10 years of follow-up beyond this time in the same way as for years 6 – 10 (section 4.5.1.2). Data will be collected on events of interest to meet primary and secondary endpoints as described in section 6.2.

Participants have been contacted by their trial site to seek their consent for follow-up beyond 10 years. This should be collected at the last PTQ visit at the year 10 post-treatment visit. Consent will be documented via completion of an electronic CRF at the trial site and can be done verbally on the phone or by paper CRF if the site posts the questionnaires for completion. The post-10-year phase of the IBIS-II trial should be considered as an additional observational element to the trial. Key safety data will nevertheless be collected as described before and reviewed as part of final study analysis, and forwarded to AstraZeneca.

Prior to the implementation of amendment 60, the above procedures were completed at all sites. Following the implementation of amendment 60, open international sites continue to follow this procedure, while patients from closed UK and international sites are followed up via digital registries as described in section 4.5.1.4.

#### 4.5.1.4 Post treatment follow up - Digital Registry Data tracking

In the UK, digital registries (NHS Digital, Public Health England (PHE), Northern Ireland Cancer Registry, National Welsh Informatics Service, NHS Services Scotland) will be used to collect follow up information relating to the cohort from month 60 until the end of their participation in the trial. These registries will provide data on cancer incidence and mortality which utilises in-patient and A&E data and national cancer registry data.

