#### **1.2 Secondary**

- 1) To examine the role of anastrozole in preventing oestrogen receptor positive breast cancer.
- 2) To examine the effect of anastrozole on other cancers, cardiovascular disease, fracture rates, and non-breast cancer deaths.
- 3) To examine tolerability and acceptability of side effects experienced by women on the study. (Met at LPLT – March 2017).

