**Table 4. Current digital dataset provision Oct 2019\***

| Organisation                            | Devolved UK Nation | HES | Mortality | Cancer Registry | Tumour markers |
|-----------------------------------------|--------------------|-----|-----------|-----------------|----------------|
| NHS Digital                             | England/Wales      | x   | x         | x               |                |
| NWIS (NHS Wales Information Service)    | Wales              | x   |           |                 |                |
| NICR (Northern Ireland Cancer Registry) | Northern Ireland   | x   |           | x               | x              |
| NSS (NHS National Services Scotland)    | Scotland           | x   |           | x               | x              |
| PHE                                     | England            |     |           | x               | x              |

\*The organisation providing data could change throughout the course of the study and a copy of this table reflecting current practice will be maintained in the IBIS-II data management plan.

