### **Scope of UK registry data collection**

Digital registry flagging is used for the UK cohort for the full duration of follow up provided valid consent (or CAG exception) is in place as described in section 4.5.5.3. While a UK site is open, registry data will be collected to confirm and underpin site-reported events. Once the site is closed, long term data collection will transition to data collection via the UK digital registries only.

HES covers all NHS Clinical commissioning groups (CCGs) in England and Wales including private patients treated in NHS hospitals, patients' resident outside of England under care provided by treatment centres, including the independent sector, funded by the NHS. For participants who commenced the study in England and moved to either Northern Ireland or Scotland, cross-border transfers will be recorded so they can be followed up via the appropriate national registry (NSS or NICR). Similarly, if participant moved from the devolved nation to England this will also be detected.

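### Registry mortality is promised for the whole UK, but Table 4 shows a mortality dataset only for England and Wales, so deaths in Scotland and Northern Ireland are likely to be under-ascertained after site closure

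*Protocol*

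**What the plan says.** Protocol section 4.5.1.4 lists NHS Digital, Public Health England, the Northern Ireland Cancer Registry, the Welsh service and the Scottish service, and says of them together: "These registries will provide data on cancer incidence and mortality". Under section 4.5.4.3 (Closed UK sites), the yearly data from the devolved registries are to be screened for deaths. Newly identified events meeting section 4.5.1.2, whose list includes deaths, go to the manufacturer once a year.

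Section 4.5.1.4 (UK Registry data sources) says that Tables 3 and 4 show what each registry will supply. The columns of Table 4 are, in order, HES, mortality, cancer registry and tumour markers. Three rows matter:

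- "NHS Digital | England/Wales | x | x | x"
- "NSS (NHS National Services Scotland) | Scotland | x | | x | x"
- "NICR (Northern Ireland Cancer Registry) | Northern Ireland | x | | x | x"

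The mortality cell is filled in the first row only. It is also blank for the separate Welsh and PHE rows, but the NHS Digital row covers those nations.

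On the period after closure, section 4.5.1.4 (Scope of UK registry data collection) says: "Once the site is closed, long term data collection will transition to data collection via the UK digital registries only".

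Deaths are needed for a secondary aim in section 1.2: "To examine the effect of anastrozole on other cancers, cardiovascular disease, fracture rates, and non-breast cancer deaths". Section 6.2 adds that total and cause-specific mortality will be analysed.

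**The concern.** The opening text of section 4.5.1.4 and the closed-site paragraph of section 4.5.4.3 assume that death data arrive from every UK nation. The by-nation table does not show this for two of them.

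The difference matters because follow-up at closed sites is passive. Where a mortality feed exists, the absence of a death record is evidence that the woman is alive. Where none exists, it says nothing. If the two situations are pooled, deaths in Scotland and Northern Ireland are under-counted and absolute mortality is understated. The deaths lost are mostly those the secondary aim is about, namely deaths of women who never had a registered cancer.

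**Working it through.** The plan gives no figure on this point to reproduce, so the check is of the text, followed by an illustration on stated assumptions.

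**Step 1. Routes by which a death could be recorded after UK site closure**

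- *Mortality dataset.* Table 4 marks it for England/Wales only. Table 3 lists civil registration mortality but names no nation, so it does not fill the blank cells of Table 4.
- *Cancer-registry records.* Table 2 lists date and cause of death, and its heading names PHE and NICR. This gives a partial route for Northern Ireland, presumably for women with a registered cancer (my inference; the protocol does not say so). Scotland is not in the heading.
- *Hospital data.* HES is marked for both nations, but the HES variables in Table 3 include no death or discharge-status item.
- *Event code list.* Section 4.5.1.4 (Data collection and storage) says that the Table 1 variables will capture deaths. Table 1 has no death item.
- *GP queries.* Section 4.5.1.4 (Following up with GPs) describes these for new or recurrent breast cancers.
- *Site reports.* These end at closure.

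So a woman in Scotland or Northern Ireland without a registered cancer has no described route to a death record. For Scotland, not even the cancer-registry route is documented.

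**Step 2. Women who move**

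The scope paragraph transfers women who move from England to Scotland or Northern Ireland to the Scottish or Northern Irish provider. As written, they pass from a source with mortality to one without.

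**Step 3. Effect on the mortality analyses (assumed inputs)**

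Let s be the share of analysed women in the two nations followed by registry only. Assume the same death rate everywhere. If none of their deaths is recorded, which is the upper bound:

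- fraction of deaths missing = s
- recorded death rate = (1 − s) × true rate, if all women stay in the denominator
- standard error of the log rate ratio is multiplied by 1/√(1 − s), because it varies as 1/√(deaths)

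The protocol does not give s. Over an assumed range:

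- s = 5%: 5% of deaths missing; 1/√0.95 = 1.026
- s = 10%: 10% missing; 1/√0.90 = 1.054
- s = 20%: 20% missing; 1/√0.80 = 1.118

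Any death captured through a cancer-registry record lowers these figures.

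**Step 4. Effect on person-time for other endpoints (assumed inputs)**

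Suppose, only to bound the effect, that every woman who died unrecorded were left in the risk set for T years. With death rate r, true mean time is t = (1 − exp(−rT))/r, and total person-time is overstated by s(T − t)/t.

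- Low end: s = 5%, r = 0.005, T = 5. t = (1 − exp(−0.025))/0.005 = 4.938. Overstatement = 0.05 × 0.0126 = 0.06%.
- High end: s = 20%, r = 0.02, T = 10. t = (1 − exp(−0.20))/0.02 = 9.063. Overstatement = 0.20 × 0.1033 = 2.1%.

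Even on that supposition, the effect on the breast cancer risk set is small. The mortality endpoints carry the problem.

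**Step 5. Effect by arm**

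Both arms use the same registries, and randomisation is stratified by hub centre in blocks (sections 3.2 and 6.1). Nation at entry should therefore be balanced, and under-recording is not expected to differ by arm.

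**The case against.** The case on the other side has several fair parts.

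- The sentence in section 4.5.1.4 speaks of the five bodies together, and goes on to say that the data draw on in-patient, A&E and cancer-registry sources. Those columns are marked for both nations. It does not promise a separate death-registration feed for each nation. This softens the contradiction. It does not supply a route for the death of a woman without a cancer record, and the closed-site paragraph still expects deaths to be found in the devolved data.
- Table 3 and the paragraph on UK data sources list civil registration mortality without limiting it to a nation. That is true, but Table 4 is the only by-nation statement, and it limits the mark to England/Wales.
- Table 4 is an October 2019 snapshot, and its footnote places the current version in the data management plan, which is not shown. The gap may therefore have been closed. The protocol text remains unreconciled, and it is what a reader has.
- Table 2 gives death fields from NICR. This stands, and makes the gap narrower for Northern Ireland than for Scotland.
- Sites report deaths while open. This stands, and confines the issue to the period after closure.

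A reader might also infer that women who have died remain in the risk set and add event-free time to every endpoint. The documents do not support this. No passage carries women without a death record to the extraction date. The only related rule, in section 4.5.1.4 (Patients lost to follow up), is written for NHS Digital non-receipt and reports women without further data as lost to follow-up. Censoring dates may be in the statistical analysis plan.

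**Conclusion.** The mismatch between the text and Table 4 is real. From the protocol as written, deaths after site closure in Scotland and Northern Ireland are likely to be under-ascertained, mainly among women without a registered cancer. That they are in fact all missed cannot be concluded from a dated table.

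The size cannot be fixed. It is tempting to derive a count of missed deaths from the 2584 participants in section 6.3, but that is a requirement across three participating countries, not a UK count, and no split by nation is given. The horizon is also unsettled: section 6.3 speaks of a further 10 years, while sections 4.5.1.3 and 6.6 run to 2022. On an assumed share of 5-20%, at most 5-20% of deaths after closure are missing, and the standard error of a mortality comparison rises by at most about 3-12%.

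No bias between arms is expected. The cost is lost precision and understated absolute mortality in the secondary aim on non-breast-cancer deaths and in total and cause-specific mortality. The primary breast cancer endpoint is not materially affected, since cancer registration is marked for both nations.

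**What to change.** 1. Reconcile the opening of section 4.5.1.4, Tables 3 and 4, and the closed-site paragraph of section 4.5.4.3. For each UK nation, name the source of date and cause of death.
2. Add death-registration data for Scotland and Northern Ireland. If the feeds already exist, update Table 4. If they cannot be obtained, correct the statement that these registries provide mortality.
3. Until the feeds are in place, either restrict registry-based mortality analyses to nations with a mortality feed, or censor women in the other two nations at site closure or last site contact, for the mortality endpoints only. State how women who move between nations are treated.
4. Leave cancer-registry follow-up for breast cancer and other cancers as it is. Censoring all endpoints at the last record would be a mistake. In passive follow-up a healthy woman generates no records, so such censoring would depend on having events and would discard valid cancer follow-up.

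The cost is a data-request variation for the two nations, some wording, and slightly fewer person-years in the interim mortality analyses. The interim rule removes the understatement of absolute mortality but does not recover precision; only the added feeds do that.
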